### Baseline Assessment

Data are collected using a standard pro forma administered by a specially trained research nurse. These include age, gender, ethnicity, educational attainment, general health status, duration of LBP, symptoms, recent treatment history, anxiety and depression (using the Hospital Anxiety and Depression Scale [29]) and employment status. In addition participants complete the baseline (pre-intervention) versions of the outcome measure package (see Table 1).

**Table 1 T1:** Outcomes measures

	Domain	Measures	Time points (months)
Primary	Pain & Disability	Roland & Morris Questionnaire (Roland 1983)	0, 3, 6, 12
	Pain	Von Korff Scale (Von Korff 1992)	0, 3, 6, 12
Secondary	Occupational and other limitations	Numbers of days off work, reduced activity and bed rest	0, 3, 6, 12
	Health related quality of life inc physical & mental health	Short Form 12 version 2 (Ware 1996)	0, 3, 6, 12
	Back Pain Beliefs	Fear avoidance scale (1^st ^five items only)* (Waddell 1993)	0, 3, 6, 12
	Self-efficacy	Pain self-efficacy questionnaire (Nicholas 2006)	0, 3, 6, 12
	Satisfaction with treatment	Single item rating of satisfaction with treatment (Deyo et al 1998)	12
Economic analysis	Resource Use	Resource use questionnaire	6, 12
	Health related quality of life; time trade off score	EQ-5D (health utility) (EuroQol Group 1990)	0, 6, 12

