### Treatment allocation

Following completion of the baseline assessment, the research nurse completes a randomisation form and telephones a central randomisation office to obtain the treatment allocation. A minimisation algorithm is used to ensure that, within each treatment arm, near equal numbers of participants are entered from each centre within the differing levels of troublesome back pain (moderately or very/extremely troublesome). The nurse provides the advice component of the intervention to all study participants, and for participants randomised to CBA, sends a notification letter to the local service provider. The service provider then contacts the participant to arrange a day/time to start the CBA treatment. Fig 1

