### Sample size

The sample size has been estimated using well-documented methods [36], with careful consideration of the practicalities to ensure that sufficient numbers of participants are randomised within an acceptable time frame. We originally planned a 1:1 randomisation ratio between CBA and usual care. Early in the trial we recognised that a 2:1 randomisation (in favour of CBA) had distinct advantages in ensuring that sufficient numbers of patients are randomised to sustain the group sessions. A randomisation balance of 2:1 can be adopted with inconsequential loss of power, but further imbalances necessitate an increase in study size. From a list size of 100,000 (approximating to one location), with twice as many participants being randomised to the intervention group, we estimated the yield of participants randomised to the group sessions was 1.4 per week, allowing us to recruit eight participants to a new group starting every six weeks. This estimate was based on data from the UK BEAM trial [37].

The potential impact of the group effect was also considered in the sample size estimation. In this trial, other effects include the individual practitioner treating several groups, regions and organisations. We perceive that the most potent of the cluster effects is the group effect, and is the only effect to have been considered formally in the sample size estimation (using methods described by [38]).

The sample size target for the trial is 700 to detect a moderate effect size, and a difference between the groups of approximately 1.8 RDQ points, assuming a standard deviation of 4.27 points (giving an effect size of 0.42). Approximately 233 participants will be randomised to active management alone and 467 participants on the active management + CBA arm of the trial. The sample size has been inflated to account for an inter-cluster correlation co-efficient of 0.01 (based on UK – BEAM [37] and incorporates a loss to follow up of 25%. We have used a power of 90% and p < 0.01 [39]. Effect sizes of approximately 0.4 are considered to be clinically worthwhile for back pain interventions [23]. The sample size requirement will be reviewed by an independent data monitoring committee at approximately the mid point of data accumulation.

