### Data analysis

Primary analyses will be by intention-to-treat, i.e. patients will be analysed in the groups to which they were randomised, regardless of the treatment that they may have received. The main study outcomes will be summarised as the Area under the Curve (AUC) over the 12 month follow up period. The AUC will be calculated by summing areas under the graph between each pair of consecutive observations for an individual. Thus the AUC is a weighted average of the outcome scores at each individual time point weighted by the time between the observations. Mean/median (depending on the distribution of the data) AUC between the two treatment groups will then be compared by a two independent sample t-test/Wilcoxon rank sum test and include reporting of the 95% confidence intervals for the mean/median difference in the AUCs. One of the advantages of the AUC method is that a sensitivity analysis may be easily performed to investigate the effect of missing data. In the case of large missing data, imputation techniques will be considered. In addition outcomes will be reported separately for the 3 month time point to characterise the early response to treatment. Multi-level modelling will be used to estimate group, therapist and other effects as appropriate.

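### The primary comparison is unadjusted and leaves open whether it targets a mean difference or ranks, so precision is lost and the estimand is not fixed

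*Protocol article*

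**What the plan says.** All places are in the protocol article.

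- **Data analysis, summary measure.** The main outcomes are reduced to an AUC over 12 months: "The AUC will be calculated by summing areas under the graph between each pair of consecutive observations for an individual".
- **Data analysis, comparison.** The AUCs "will then be compared by a two independent sample t-test/Wilcoxon rank sum test". No covariate is named. The quantity to be compared is given as "Mean/median (depending on the distribution of the data) AUC between the two treatment groups", and no rule or threshold for choosing between the tests is given.
- **Data analysis, modelling.** "Multi-level modelling will be used to estimate group, therapist and other effects as appropriate". This neither replaces the test above nor names baseline score, centre or troublesomeness.
- **Baseline Assessment.** "participants complete the baseline (pre-intervention) versions of the outcome measure package". Table 1 lists both primary outcomes (Roland and Morris, Von Korff) at months 0, 3, 6 and 12.
- **Treatment allocation.** Minimisation is used so that "near equal numbers of participants are entered from each centre within the differing levels of troublesome back pain".
- **Sample size.** The planning quantity is a mean difference: "a difference between the groups of approximately 1.8 RDQ points", with an SD of 4.27.

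**The concern.** Three features of the stated comparison work against the trial.

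1. **The target is open.** A t-test addresses the difference in means. The rank sum test addresses whether scores in one arm tend to exceed those in the other, and compares medians only under a pure location shift. Until the distribution has been seen, the reader does not know which quantity is primary. Only one of the two is the quantity the trial is sized on.
2. **The baseline score is not a covariate.** It is measured on everyone before randomisation and probably predicts later scores. Leaving it out widens the interval and leaves any chance baseline difference in the estimate. If month 0 is one of the AUC observations, the baseline score is also part of the outcome itself.
3. **The minimisation factors are not covariates.** Balancing on centre and troublesomeness removes their contribution from the true variance of the difference. An unadjusted standard error still counts it.

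At stake are interval width and a clear primary estimand.

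**Working it through.** **Plan's own figure.** 1.8/4.27 = 0.42, as stated. With two-sided alpha 0.01 (sidedness is not stated), 90% power and 2:1 allocation, the control arm needs 1.5 × (2.576 + 1.282)² / 0.4215² ≈ 126, so 378 in total. Multiplying by 1 + (m − 1) × 0.01 for groups of m = 6 to 8 and dividing by 0.75 gives 529 to 539, not 700. That mismatch is a separate matter. Here it means only that power is above plan. With 700 randomised and 25% lost, about 175 and 350 are analysed. At m = 8 the SE is 4.27 × √(1/175 + 1/350) × √1.07 = 0.409, and 1.8/0.409 − 2.576 = 1.83, which is about 97% power.

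**AUC weights.** By the trapezoid rule on months 0, 3, 6 and 12, divided by 12, the weights are 0.125, 0.25, 0.375 and 0.25. On months 3, 6 and 12 only, divided by 9, they are 1/6, 1/2 and 1/3.

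**Gain from baseline adjustment.** Assume equal variance at each visit, correlation a between baseline and each follow-up, and correlation c between follow-ups. None of these is in the article. In units of the single-visit variance:

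- Month 0 in: var = 0.28125 + 0.21875a + 0.5c; covariance with baseline = 0.125 + 0.875a.
- Month 0 out: var = 0.3889 + 0.6111c; covariance with baseline = a.
- R² = covariance²/var; cut in SE = 1 − √(1 − R²).

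Example with a = c = 0.5 and month 0 in: var = 0.641, covariance = 0.5625, R² = 0.494, cut = 1 − √0.506 = 29%.

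| a | c | Month 0 in: R², cut in SE | Month 0 out: R², cut in SE |
|---|---|---|---|
| 0.4 | 0.4 | 0.397, 22% | 0.253, 14% |
| 0.5 | 0.5 | 0.494, 29% | 0.360, 20% |
| 0.7 | 0.7 | 0.693, 45% | 0.600, 37% |
| 0.4 | 0.7 | 0.314, 17% | 0.196, 10% |
| 0.3 | 0.7 | 0.215, 11% | 0.110, 6% |

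At a = c = 0.5 the gain is worth a sample 1/0.506 = 1.98 times as large with month 0 in, or 1/0.64 = 1.56 times with it out.

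**Dilution.** With month 0 in, a constant post-baseline effect of 1.8 appears as 0.875 × 1.8 = 1.58. Adding baseline as a covariate does not undo this 12.5% shrinkage; taking month 0 out of the AUC does.

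**Minimisation factors.** If they explain a share f of the outcome variance and are well balanced, the true SE is √(1 − f) times the reported one, and the true type I error is 2[1 − Φ(z/√(1 − f))].

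| f | True error at nominal 5% | True error at nominal 1% |
|---|---|---|
| 5% | 4.4% | 0.8% |
| 10% | 3.9% | 0.7% |
| 20% | 2.8% | 0.4% |
| 30% | 1.9% | 0.2% |

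A null simulation (6,000 runs, 525 analysed, 2:1, permuted blocks within centre by troublesomeness standing in for minimisation) agreed within its error. The test adjusted for both factors kept about 5% and 1%. The article does not give f.

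**The case against.** - **The comparison is valid as it stands.** An unadjusted comparison of randomised arms is unbiased, and chance baseline imbalance is already reflected in its confidence interval. This stands. A reader might infer that ignoring the minimisation factors inflates false positives. It does the reverse: the standard error is too large, and only slightly so if the factors predict little. A small offset runs the other way. A plain t-test also ignores therapy-group clustering, which at ICC 0.01, groups of 8 and clustering in the CBA arm only understates the variance by about 2% ((2 + 1.07)/3 = 1.023).
- **The gain may be modest.** Inclusion of month 0 is the literal reading of the trapezoid rule with Table 1, but it is not stated outright. Eligibility requires at least moderate troublesomeness, which may narrow the baseline range and weaken its correlation with follow-up. Both points stand and are why the range is wide.
- **Power is not short.** This also stands; a reader might infer that the trial is underpowered, and the stated inputs do not support that.
- **The choice of test may be made blind.** The text does not say that the distribution would be inspected by arm or unblinded, so a charge of choosing the test on results is unsupported. What remains is that no rule is given and the two tests answer different questions.
- **Adjustment may be in an unseen SAP.** Covariate lists often are. Here, however, the article writes out the primary test, and its modelling sentence does not replace it.

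**Conclusion.** The point holds as one about a fixed estimand and lost precision; it is not a claim of bias, excess false positives or inadequate power. The stated comparison leaves mean or rank undecided, although the trial is sized on a mean difference, and it omits three pre-randomisation variables that are already collected. Baseline adjustment would cut the standard error by 22–45% (month 0 in the AUC) or 14–37% (month 0 out) under equal between-visit correlations of 0.4 to 0.7. The cut would be about 6–17% if baseline correlates at 0.3 to 0.4 with follow-ups that correlate at 0.7 with each other. All of these correlations are assumptions. The conservatism from omitting the minimisation factors depends on how prognostic they are, which the article does not say. The change is worth making but is not critical to the trial's validity.

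**What to change.** Pre-specify one primary analysis: a linear mixed model for the mean difference in the AUC (time-averaged score) of the post-baseline measurements. Adjust it for the baseline value of the same outcome, centre and troublesomeness level, and include a therapy-group random effect in the CBA arm. Taking month 0 out of the outcome and using it as a covariate removes the 12.5% dilution as well as the lost precision. Delete the t-test/Wilcoxon switch. With about 175 and 350 analysed, a mean comparison does not need it. If skewness is a worry, report a bootstrap interval for the same mean difference, or a rank test, as a sensitivity analysis only.

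The cost is wording in the analysis section. All the covariates are collected before randomisation, and no change to data collection or sample size is needed.

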### Sub-group analyses

The potential biases inherent in undertaking multiple sub-group analyses are well recognised [40]. However, the BeST trial offers a unique opportunity to generate hypotheses about the profile of patients most likely to benefit from group based CBA. The most scientifically robust method of sub-group analysis is a test of interaction between treatment and outcome that has been appropriately powered. It is widely recognised that powering a sub group analysis can dramatically increase sample size requirement. A rough rule is that detection of interactions approximately twice the size of the main effect requires no increase in the sample size, provided that the sub-groups are of equal size, the sub-group comparisons are limited and pre-specified, and the results are considered hypotheses generating as opposed to confirmatory [40]. We will report two pre-specified analyses alongside the main trial results, namely a comparison of treatment effect in those groups

i) with sub-acute versus chronic low back pain at study entry.

ii) with moderately versus very/extremely troublesome back pain at study entry.

iii) With high versus low fear avoidance at study entry.

These comparisons assume that detection of large effects, and that sub-groups are of roughly equal size.

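### The subgroup plan promises two pre-specified analyses but lists three, misnames the interaction, and reduces a baseline fear-avoidance score to high versus low

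*Protocol article*

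**What the plan says.** All of this is in the protocol article, Sub-group analyses.

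- The method is named once: "The most scientifically robust method of sub-group analysis is a test of interaction between treatment and outcome that has been appropriately powered".
- The commitment is "We will report two pre-specified analyses alongside the main trial results", for a comparison of the treatment effect between groups defined at entry. Three items follow: (i) "with sub-acute versus chronic low back pain at study entry", (ii) "with moderately versus very/extremely troublesome back pain at study entry" and (iii) "With high versus low fear avoidance at study entry".
- The power argument is a rough rule that "detection of interactions approximately twice the size of the main effect requires no increase in the sample size". Its conditions are that the subgroups are equal in size, that comparisons are few and fixed in advance, and that results are treated as hypothesis generating.
- The section closes: "These comparisons assume that detection of large effects, and that sub-groups are of roughly equal size".

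Elsewhere, Eligibility criteria sets a minimum pain duration of six weeks with no maximum. Table 1 schedules the fear avoidance scale at month 0. Baseline Assessment lists pain duration without a response format.

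**The concern.** A subgroup claim is credible only if the reader can tell which comparisons were fixed beforehand. Here the count and the list disagree, and nothing says which item is the extra one. The section makes its power rule conditional on a limited, pre-specified set, so the mismatch touches its own premise. A later report could present two or three analyses and claim to follow the protocol either way.

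The question is also a stated interest of the trial: the Background says there is a need to learn whether baseline characteristics predict response. That makes two further points worth attention. Cutting the fear-avoidance score into two groups gives up information already collected. And the power rule needs halves of similar size, which an open-ended duration criterion may not deliver for sub-acute versus chronic pain.

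**Working it through.** **1. Count and wording.** Announced: two. Listed: i, ii and iii. If the tests were independent at 0.05 (an assumption), the chance of at least one false positive is 1 − 0.95² = 9.8% for two and 1 − 0.95³ = 14.3% for three. The named interaction, "a test of interaction between treatment and outcome that has been appropriately powered", pairs treatment with the outcome. The same section speaks of treatment effects compared between groups defined at entry, so treatment by baseline factor is plainly what is meant.

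**2. The plan's own rule.** With a smaller subgroup of share p, SE(interaction) = SE(main) × √(1/p + 1/(1−p)). At p = 0.5 the factor is √4 = 2. An interaction twice the main effect therefore has exactly the main-effect power. The rule reproduces.

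**3. Unequal subgroups.**

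Inputs from Sample size: difference 1.8 points, SD 4.27, arms of 233 and 467, 25% loss, intra-cluster correlation 0.01. From Experimental intervention: groups of up to 8. Assumptions: two-sided tests, the stated SD applies to the analysed outcome, and the shares p, since the article gives none.

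- Evaluable: 233 × 0.75 = 174.75 and 467 × 0.75 = 350.25.
- Design effect in the CBA arm: 1 + (8 − 1) × 0.01 = 1.07.
- SE(main) = 4.27 × √(1/174.75 + 1.07/350.25) = 0.400.
- Target interaction: 2 × 1.8 = 3.6 points.
- Power = Φ(3.6/SE(interaction) − z), with z = 2.576 at 0.01 and 1.960 at 0.05.

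| Smaller share p | Factor | SE(interaction) | Power, alpha 0.01 | Power, alpha 0.05 |
|---|---|---|---|---|
| 50% | 2.00 | 0.80 | 97.3% | 99.4% |
| 25% | 2.31 | 0.92 | 90.7% | 97.4% |
| 20% | 2.50 | 1.00 | 84.7% | 94.9% |
| 15% | 2.80 | 1.12 | 73.8% | 89.5% |
| 10% | 3.33 | 1.33 | 54.9% | 77.0% |

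The interaction detectable with 90% power at 0.01 is (2.576 + 1.282) × SE: 3.09 points at 50%, 3.86 at 20% and 5.14 at 10%. At 0.05 and 15% it is (1.960 + 1.282) × 1.12 = 3.63 points, almost exactly the target.

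These figures use 700 randomised, which is more than the stated inputs need. They give 378 evaluable, and with the design effect on both arms 378 × 1.05/0.75 = 529 (groups of 6) to 378 × 1.07/0.75 = 539 (groups of 8). In a trial sized exactly for 90% at 0.01, power for the doubled interaction would be 90% at an equal split, 70% at 20% and 40% at 10%.

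**4. Which factors could be unequal.**

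- Duration: the only boundary in the article is in the Background, where acute means under three months. If that also divides sub-acute from chronic (an assumption), sub-acute spans about 13 − 6 = 7 weeks against an open-ended chronic group.
- Troublesomeness: both levels are eligible, and nothing points to imbalance.
- Fear avoidance: no entry criterion applies, and a median split gives halves.

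**5. Dichotomising.** For a normally distributed score that modifies the effect linearly, a median split retains 2/π = 0.637 of the information. With 700 × 0.75 = 525 evaluable, that equals using the continuous score in about 0.637 × 525 = 334 people.

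**The case against.** The section is candid. It states the equal-size condition twice, says that only large effects are in view, warns of the biases of multiple subgroup analyses, and treats the results as hypothesis generating. The interaction slip should mislead no careful reader. All three factors were published while recruitment was still open, so reporting the third would not pass off a post hoc analysis as planned; the remaining risk is that one is dropped without notice. The fear-avoidance cut-point may be in an analysis plan that is not shown, so its absence is no fault. All of this stands, and it keeps the point modest.

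A reader might go further and infer that the entry criteria undermine the equal-size premise for the whole plan, so that the planned tests lack the power claimed. The documents do not support that. The argument reaches one factor of three. Even there, the article gives no boundary and no share, and besides the record search it recruits patients identified by practice staff at attendance, who could include recent-onset cases. Nor does it set a significance level for subgroup tests: 0.01 belongs to the main sample size, and Data analysis reports 95% intervals. At 0.05 a 15% share still gives about 90% power.

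It could also be said that continuous modifiers are a preference. That is partly so: the gain depends on the modifier acting roughly linearly.

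**Conclusion.** Two textual errors are certain: two analyses announced against three listed, and an interaction named with the outcome in place of a baseline characteristic. The first matters because it leaves the pre-specified set ambiguous; the second is clerical.

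Testing fear avoidance as high versus low is an avoidable loss, about 36% of the information under a median split, normality and linearity.

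The equal-size premise is doubtful for duration alone, and by inference. With 700 randomised and 25% lost, it costs material power for a 3.6-point interaction only if the smaller share is about 20% or less at two-sided 0.01, or below about 15% at two-sided 0.05. A general claim that the subgroup tests are underpowered does not follow.

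**What to change.** 1. State three pre-specified analyses, or name the one that is dropped.
2. Replace the phrase with interaction between treatment and the baseline characteristic.
3. Test the fear-avoidance interaction with the continuous month-0 score in a regression model for the AUC outcome, and show high and low effects for description only. The planned t-test or Wilcoxon comparison has no place for an interaction term, so this is an added model. Treat duration in the same way only if it was recorded on a continuous scale.
4. Confine the equal-size caution to the sub-acute versus chronic comparison, and judge that comparison by the confidence interval of its interaction.

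The cost is a few words and a small regression analysis, with no new data for fear avoidance. The downside is a linearity assumption, which can be checked graphically.
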